#### Additional analyses

As a sensitivity analysis the primary endpoint will be evaluated based on the per-protocol set of patients without major protocol violations. Additional sensitivity analyses will be done using LOCF and complete case analysis via analysis of covariance (ANCOVA) for repeated measurements. Safety analysis includes calculation and comparison of frequencies and rates of (S)AEs.

*Analysis of predictors and moderators*: in an exploratory fashion, implementing the above–mentioned MMRM approach, including the pre-specified variables as main or interaction effects in the respective models. For each pre-specified variable an own model will be calculated.

*Treatment mechanism* on the primary efficacy endpoint will be investigated following the mediation analysis approach described in Pickles et al. 2015 [28].

All analyses will be done using SAS® version 9.4, except for utilising Mplus software for the investigation of treatment mechanism.

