### Design

The trial is designed as a confirmatory, phase-III, prospective, randomised, multi-centre, controlled, parallel-group study with two treatment arms and six measurement time points. The trial time flow is shown in Fig. 1.

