### Setting

The study will take place in a clinical setting at four German study centres which provide a special outpatient service for individuals with ASD (University-based Departments of Child and Adolescent Psychiatry, Psychosomatics, and Psychotherapy at Augsburg, Dresden, Frankfurt and Würzburg). The sponsor is the Goethe University Frankfurt (GU), and the principal investigator is [name]. [name], University Hospital Frankfurt at GU. The study-related diagnostic tests for all children (A-FFIP and EIAU) are performed at the four study centres, and are coded in a blinded fashion by independent individuals who are not involved in any intervention. A-FFIP is delivered by two therapists/child at the four study centres, who are not involved in any study-related diagnostic procedures. EIAU is delivered in any local setting outside the four study sites.

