#### Setting

Sessions are provided in an outpatient setting at the respective study centre. All treatment rooms are furnished in a standardised way, with standardised and well-arranged play material, ensuring a structured environment providing orientation and a minimum of distraction.

The intervention comprises 2 h of intervention/week with two therapists working with the child. The two-therapist concept is an essential A-FFIP component. While the main therapist interacts with the child, the co-therapist acts as a shadow and prompts the child individually and in a situation-specific way, during the learning of new abilities, and only if necessary. This concept is believed to support the natural learning of the child, because the child will learn the specific skill or task faster, and the interaction with the main interaction partner (therapist/parent) is independent from any prompting efforts. If the child is very advanced and shows interest in social interaction with peers, two therapists will work with two equally advanced children. At least one parent is participating in a minimum of every fifth therapy session for psychoeducation and exercises with their individual child, with the aim of learning to use effective strategies for practising at home. Parents are asked to practise established skills at home in many naturally occurring situations; these tasks are determined by the therapist and the implementation is discussed regularly with the parents. To ensure compliance by supporting parents without increasing pressure, no specific amount of practising hours or situations is expected. Parental adherence and competence is assessed by a weekly questionnaire (PATCS, see section ‘Mediating mechanisms’).

If the child already attends kindergarten, one therapist visits the child’s kindergarten teachers, and (if existing) the personal assistant three times a year for individualised psychoeducation with the aim to support generalisation of the child’s acquired skills at kindergarten. The first appointment is organised directly at the beginning of the intervention.

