### Control intervention: early intervention as usual (EIAU)

For EIAU, individual or group therapy intensity of 1–10 h/week as well as waiting time prior to any intervention onset is allowed. This is representative for the German ASD preschool population, and comparable average intervention intensity per week is expected for both groups with higher variability for EIAU than A-FFIP [47].

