### Predictors and moderators

IQ/DQ, BOSCC-AT, gender, ADI-R and both parent‘s educational status will be investigated. The educational status will be classified according to the *International Standard Classification of Education (ISCED)* 2011.

An eye-tracking battery will be applied at T2, T4 and T6. This *eye-tracking battery* includes measures of sensory perception and visual orientating preferences. These tasks include: pupil adaption fixation stability (PAFS), smooth pursuit (SMT), visual oddball (VOT), visual search (VST), non-social versus social reward (NSRT), dynamic emotion expressing faces (DEEF), natural scenes (NST), biological motion visual preference (BMVP) and joint attention task (JAT).

*Spontaneous imitation* is assessed by automated-movement analysis via depth sensor cameras during video-based assessments (ESCS, BOSCC, DCMA, ADOS-2).

*Parental treatment attendance* will be documented weekly by therapists [74].

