### Harms

As A-FFIP is a psychotherapeutic intervention, a very low frequency of (S)AEs is expected. Nevertheless, a Data and Safety Monitoring Board (DSMB) will be installed and safety relevant events will be reported to this board. Based on the recommendations of the DSMB, the study might be stopped. All (S)AEs that occur after the subject has signed the informed consent document will be documented on the pages provided in the CRF. SAEs must be reported to the principal investigator within 24 h after the SAE becomes known using the ‘Serious Adverse Event’ form. The investigator must also inform the site monitor in all cases. The investigator is responsible for notification of SAEs to the responsible institutional review board. Patients with SAEs will receive regular medical care in the public health care system.

Patients and their legal representatives will be insured for travel to the way to the regarding study centre (Reference number: F-W20; File number: 2330 991,102; ECCLESIA mildenberger HOSPITAL GmbH).
Cover in case of death: 50,000 EuroCover in case of invalidity: 100,000 Euro

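### The planned between-arm comparison of adverse-event rates could partly reflect better detection in A-FFIP, because only that arm has weekly contact with the study centres

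*Protocol article*

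**What the plan says.** The safety analysis is fixed in one sentence of the Protocol article, Additional analyses: "Safety analysis includes calculation and comparison of frequencies and rates of (S)AEs". The Harms section sets the recording rule, in the same words for both arms: "All (S)AEs that occur after the subject has signed the informed consent document will be documented on the pages provided in the CRF". For serious events, the 24-hour reporting period starts when the event comes to be known. The same section expects very few events of either kind, without giving a figure.

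Contact with the study centres differs by arm:

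- **A-FFIP.** The Setting section of Methods/design says "A-FFIP is delivered by two therapists/child at the four study centres, who are not involved in any study-related diagnostic procedures". The Setting section on the intervention adds "The intervention comprises 2 h of intervention/week with two therapists working with the child". Therapists complete a progress form after each session (Individualised treatment targets). Parental attendance "will be documented weekly by therapists" (Predictors and moderators). A parent joins at least every fifth session, and parents complete a weekly questionnaire on adherence and competence.
- **EIAU.** "EIAU is delivered in any local setting outside the four study sites" (Methods/design, Setting). The section on the control intervention adds: "For EIAU, individual or group therapy intensity of 1–10 h/week as well as waiting time prior to any intervention onset is allowed".
- **Both arms.** The Design section describes "two treatment arms and six measurement time points".

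Under Blinding, the article says that parents and therapists cannot be blinded.

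**The concern.** An adverse event enters the database only if someone connected with the trial learns of it. In A-FFIP that can happen at a weekly session or at an assessment. In EIAU, on what the article describes, it happens mainly at an assessment, where it depends on what the parent recalls over a longer interval. If all recorded events are compared, the two arms are counted under different levels of observation.

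The likely direction is against A-FFIP: with no true difference in harm, its recorded rate could be higher. If there were a true difference, the recorded ratio would not give its size. This matters most for non-serious events, which are easily forgotten. Serious events such as hospital admissions are less likely to be missed, so the six-monthly reports of serious events to the safety board should be affected much less.

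**Working it through.** **Inputs from the article.** 67 children are randomised per arm (Sample size calculation). The arithmetic there reproduces: a two-sample t test at effect size 0.55, two-sided 5% and 80% power needs 53 per arm, and 53 / (1 − 0.20) = 66.25, rounded up to 67. The present point does not affect it. The article gives no adverse-event rate and no detection probability, so every value of these below is an assumption.

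**Step 1: contact.** Sessions total 2 h per week. If that means one session a week, there are about 50 session contacts per child-year in A-FFIP. At the required minimum of every fifth session, a parent is present at about 50 / 5 = 10 of them. The contact described for both arms is six measurement points in all. Session contact starts only when A-FFIP starts, and Additional treatments and medication use allows for a wait beforehand.

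**Step 2: what the recorded ratio measures.** Recorded rate = true rate × detection probability. With equal true rates, the true rate cancels:

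recorded ratio = detection in A-FFIP / detection in EIAU

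With detection of 0.9 in A-FFIP (assumed):

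- EIAU 0.7: 0.9 / 0.7 = 1.29
- EIAU 0.5: 0.9 / 0.5 = 1.80
- EIAU 0.3: 0.9 / 0.3 = 3.00

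The ratio is distorted in this way whatever the event rate.

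**Step 3: would it produce a significant difference?** The article names no safety test, so Fisher's exact test at two-sided 5% is used only as an illustration, with 67 per arm. Expected recorded count = 67 × true risk × detection. For example, 67 × 0.05 × 0.9 = 3.0 children in A-FFIP and 67 × 0.05 × 0.7 = 2.3 in EIAU.

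| True risk, both arms | Expected A-FFIP (0.9) | Expected EIAU (0.7 / 0.5 / 0.3) | Chance of p < 0.05 (0.7 / 0.5 / 0.3) |
|---|---|---|---|
| 5% | 3.0 | 2.3 / 1.7 / 1.0 | 1% / 2% / 3% |
| 10% | 6.0 | 4.7 / 3.4 / 2.0 | 3% / 7% / 17% |
| 30% | 18.1 | 14.1 / 10.0 / 6.0 | 9% / 33% / 73% |

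With equal detection of 0.9 in both arms, the chance is 1% to 3% over these risks. At a 5% risk it stays at 3% or below even under the most unequal detection. It becomes large only if events are common and detection is very unequal.

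**The case against.** The strongest objection is that the article does not say how, when or by whom adverse events are elicited. That detail commonly sits in the full protocol, which is an additional file and not shown, or in the analysis plan. Either may prescribe the same questioning of all families at T1 to T6. Where the article does give a schedule for health data, it is common to both arms: drug treatment is documented at each assessment. This stands as far as the missing schedule goes, and that absence is not the point here. It does not settle the matter, because events learned of between assessments also count under a rule that has all events documented, and one arm has far more occasions for that.

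Four stronger readings are tempting, and the documents do not support them:

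- *Therapists act as adverse-event collectors.* No section says so. Their forms record progress on treatment targets and parental attendance, and they take no part in study diagnostics.
- *About 50 surveillance contacts stand against a handful.* Parents are the likely informants for children of this age and need attend only every fifth session.
- *A-FFIP will be declared less safe.* That needs frequent events and a formal test. The article expects very few events, and its 5% level is set for the primary endpoint. The comparison may be purely descriptive.
- *Session-learned events should be dropped from the arm comparison altogether.* Removing genuine events from the only comparative table would be a reporting loss of its own.

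**Conclusion.** The point holds in a limited form. The article plans to compare recorded event rates between arms that it describes as having unequal contact with the study centres, so those rates could partly reflect detection as well as harm. The effect would fall mainly on non-serious events and much less on serious ones.

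Its size cannot be taken from the documents. The ratio of 1.29 is an illustration that rests on assumed detection of 0.9 and 0.7 and on equal true rates. If events are as rare as the article expects, a falsely significant difference is unlikely; the consequence is a ratio that is hard to interpret. A reader might infer that the safety comparison is invalid or that the trial's conclusions are at risk, but neither follows. The comparison is not confirmatory, and the primary analysis does not depend on it.

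**What to change.** Keep the table of all adverse and serious adverse events by arm, and state beside it that ascertainment was unequal. Base the between-arm comparison of non-serious event rates on events elicited by the same question, with the same recall period, at the assessments that both arms attend. An event first mentioned at a session and also reported at the next assessment belongs in this comparison. Mark events learned of only through A-FFIP sessions separately.

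This takes a sentence or two in the safety analysis and a source field on the adverse-event form. Recruitment began in April 2018 and was planned to finish in 2019, so some events will have been recorded without that field. For these, use the date and place of first report where available. Classifying by first report is only a fallback: it can drop A-FFIP events that the parent would also have reported at the assessment, so it should be read next to the all-events table.

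The downside is that the restricted comparison uses fewer events and is less precise. It also leaves any reporting difference that comes from unblinded parents. No event is lost from reporting, and expedited reporting and safety-board oversight are unchanged. Label: cheap improvement.

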## Discussion

The present randomised controlled, multi-centre, parallel-group trial including an active control group aims at establishing efficacy of the manualised A-FFIP early intervention programme for toddlers and preschool-aged children with ASD on ASD-specific symptom change after 1 year. As stated in the introduction, A-FFIP has been developed on a strict empirical basis as a low-intensity, comprehensive, individualised early intervention, which is unique in the field of early intervention in ASD.

The design of the study addresses a number of relevant issues in ASD-specific early intervention research and also aims to overcome limitations of previous studies, i.e. study quality [83], questionable use of primary outcome measures [42] and missing moderator analyses [32].

Study quality is ensured by a number of specific procedures. First, intensive training in the relevant diagnostic instruments, such as ADOS-2, BOSCC, ESCS and DCMA, will be provided by the Frankfurt study group. Video-based ratings prior to study start will be done to ensure full objectivity of the testing procedure. Similarly, an intensive training in the manualised A-FFIP intervention is provided by the first author of A-FFIP and long-standing A-FFIP experts in the Frankfurt group. The training is accompanied by ongoing video-based feedback prior to, and during, intervention. Therapists need to meet pre-specified criteria regarding their therapy-related competencies before being allowed to treat the children within the study and will be supervised regularly during the study period. Most high-quality studies in early intervention, such as PACT [14, 84] and ESDM [11], reported on their training procedures, which are, overall, comparable with the one implemented in the present study.

Second, during the study, the primary and secondary video-based outcome measures (BOSCC, DCMA, ESCS, ADOS-2) are rated by a small Frankfurt-based team, with established high inter-rater reliability and ongoing consensus ratings, to reduce the risk of measurement errors. The diagnostic team leader has received training on the BOSCC and the DCMA by the developer of the regarding instruments, before. This procedure has also been reported in similar intervention studies [44, 84, 85].

Third, as recommended by the International Council for Harmonisation of Technical Requirements for Pharmaceuticals for Human Use – Good Clinical Practice (ICH-GCP) [86] data management, study monitoring and statistical analyses are done by independent institutions, specialised in their respective field. The ICH-GCP standard has rarely been implemented in psychotherapy trials, despite its major role in European pharmaceutical trials.

By choosing the BOSCC as the primary outcome measure, changes in ASD-specific behaviour are investigated by a change-sensitive instrument. The BOSCC will be done in a standardised and blinded fashion [24, 44]. The chosen BOSCC testing situation with a foreign person will also add information about generalisation of acquired competencies. Previous studies have chosen different primary outcome measures. In most studies, in which distant outcome measures were used, especially cognitive (i.e. IQ measures), language or non-blinded measures of adaptive abilities (i.e. Vineland Adaptive Behaviour Scales, VABS) were chosen as primary outcome [12, 42, 87].

Thus, many early intervention studies do not give any information on the central question of intervention in ASD, namely the improvement of core ASD symptoms. In addition, most studies did not use blinded outcome measures, especially such studies, which have implemented parent-based questionnaires as primary outcome measure, such as the VABS.

Only one multi-centre RCT has used the blinded ADOS as primary outcome to describe change in core ASD symptoms [14, 84]. In the primary analysis, no change of core ASD symptoms was observed. This likely is due to the character of the ADOS, which was not designed to measure behaviour change over time, but as a diagnostic instrument [42]. The BOSCC has been developed based on the ADOS, but with a revised scoring system and additional items, thus showing higher measurement variability and sensitivity to change [48]. It is currently also implemented in several studies internationally [84, 85].

Additional, the secondary outcome measures of the present study will allow the detection of change in the child’s cognitive and, language development, additional internalising and externalising psychopathological symptoms, and A-FIPPs’ effects on parent’s behaviours, family well-being and quality of life.

Using these various secondary outcomes allows a direct comparison with other studies, such as cognitive and language development within the ESDM study [11], or gain in parental self-efficacy (questionnaire) and parental synchrony (DCMA) within the PACT study [84]. In addition, several family related measures have been added which have rarely been reported in previous studies, meeting the expectation of the parents on relevant outcome measures [42].

The unique, low-intensity, but complex and comprehensive NDBI concept of A-FFIP also adds valuable information to the discussion about needed treatment intensity for children with ASD [16, 88]. Low-intensity approaches can be delivered to more families compared to high-intensity approaches, and might be more cost-effective than high-intensity approaches. Additionally, recent studies have shown that some comprehensive, high-intensity approaches did not lead to change in core ASD symptoms [12], but focussed, low-intensity approaches (as in the PACT study [14, 23]) achieved long-time changes in ASD-specific behaviour. Future studies may focus on the clinical relevance of the respective changes, and efficacy and cost-effectiveness studies should directly compare low- and high-intensity approaches.

Regarding predictors and moderators of intervention outcome, most frequently age, IQ, or ASD-specific symptoms prior to the start of the intervention, have been studied as possible predictors or moderators of treatment outcome [32]. This also will be done in the present study. In addition, the objective measures implemented, such as eye-tracking and objective movement parameters are unique, and will provide important additional information on ‘what works for whom’ [36]. This may also allow us to partly explain the variability in outcomes of early intervention trials.

The analysis of mediators will allow an exploratory therapy process analysis. Child-specific as well as parent- and therapist-specific characteristics will be explored as mediators, such as the child’s learning curve on essential abilities as joint attention. Therapist fidelity is regularly assessed which allows us to specifically elicit the role of the therapist-related competencies on intervention outcome. Parental treatment adherence and competence are assessed by a weekly questionnaire (PATCS) filled in by the parents, on their self-rated ability to implement the learned strategies in their daily routine. A-FFIP is conceptualised as a low-intensity, therapist-delivered programme, in which parents are regularly supported to encourage the generalisation of new, individually meaningful and developmentally appropriate skills in daily, natural routines. The extent of parental involvement is adjusted to the individual’s familiar needs and resources. In addition, child-specific psychoeducation is provided for kindergarten teachers. Parents and kindergarten teachers are not expected to do particular exercises with the child. Future studies might focus on more objective fidelity measures of the parental implementation of intervention methods and targets at home. In the current study, the parent rating questionnaire will provide data on the parent’s sense of satisfaction, competence and intensity using A-FFIP strategies at home. This information will again be explored as a possible mediator of therapy outcome.

If efficacy is shown, additional expected positive effects by the trial will be: (1) Improvement of care in underserved areas in Germany (such as Bavaria, Saxony); (2) Alerting many different professionals working in early intervention in ASD to effective methods and (3) Establishing an effective training and supervision method provided to professionals to achieve high treatment fidelity of evidence-based early intervention. Thus, the current study may change clinical practice strongly towards the implementation of evidence-based early intervention methods in ASD in Germany. Because A-FFIP is delivered through two therapists for a 2-h/week intervention it may also be applicable in other areas with comparable public health systems. Therefore, the study results should be of great impact for many ASD underserved regions.

